# Background

Mobilisation alarms are a staple in hospitals as part of the falls prevention management repertoire, they can take up to 11% of all falls prevention management costs (Mitchell et al., 2018). However, a 2018 Cochrane review conducted a meta-analysis that found “uncertain evidence of the effects of bed and chair sensor alarms in hospitals” (Cameron et al., 2018). The review’s statistical findings suggested that there may be benefits the use of alarms in reducing falls rate, but this is not definitive. This is a problem as a wide-spread practice with uncertain effectiveness can use up resources that would be better spent on known effective practices or developing innovative approaches. Based on a recent study conducted by Monash University in 6 Victorian health services, the cost of purchasing, application, and staffing mobilisation alarms consume over 4.5 million Australian Dollars per annum (Mitchell et al., 2018). Closer examination of the use of these alarms has also highlighted impacts on nursing staff and patients. Nursing staff have reported to experience anxiety related to the use of alarms, and have to disrupt important tasks at hand to respond to alarms (King, Pecanac, Krupp, Liebzeit, & Mahoney, 2018), which may lead to detrimental errors in delivery care (Westbrook, Woods, Rob, Dunsmuir, & Day, 2010) and abandonment of tasks (Westbrook, Coiera, et al., 2010). Although not a physical restraint, the alarms have been cautioned by experts as a form of restraint on patients (Inouye, Brown, & Tinetti, 2009), which not only do not reduce falls but can also lead to other adverse outcomes (Lach, Leach, & Butcher, 2016). **Disinvestment** was proposed as a method to address the uncertainties in falls prevention strategies (Mitchell et al., 2018).

The term “***disinvestment***” is defined as the ***displacement of non–cost-effective approaches for resource reinvestment or reallocation*** (Joshi, Stahnisch, & Noseworthy, 2009). To maximise efficiency and effectiveness of research, we propose the disinvestment process be integrated with a stepped-wedge design, where wards begin with usual practice and are phased into the disinvestment condition over time in random order; non-inferiority margin stopping rules will be set to ensure maximum safety. This approach allows for comparisons within and between wards across time, and gives participating health professionals and service managers to contribute to the determination of stopping-rules during the trial. In doing so, the proposed study will produce robust findings of the effectiveness of mobilisation alarms, the effectiveness of the disinvestment process, and the economic efficiency of the process on mobilisation alarms. The outcomes will also go on to provide an efficient model for health service quality assurance projects in Australia and world-wide.

The four stages of disinvestment are 1) identification of low-value practices, 2) facilitate the disinvestment process, 3) evaluate outcomes, and 4) sustain the disinvestment (2). As the potential low-value practice has already been identified as mobilisation alarms. This proposal will detail steps 2 to 4 in a trial with a stepped-wedge design.

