## Methodological Approach

This will be a concurrent, nested, randomised stepped-wedge study with a mixed methods and non-inferiority design (Figure 1). Half of the wards (n=18) will be assigned to the intervention arm, the other half to the control arm. All wards in the intervention arm will begin under the same “usual care” condition, pairs of wards will begin the disinvestment condition at different time points, which will allow for comparisons of the ward with itself under different conditions: a) usual care of utilising the mobilisation alarms, and b) removing or reducing its use. Randomisation will determine whether each ward undergoes a removed or reduced mobilisation alarm condition, and the timing at which they phase into this condition. All wards in the control arm will be observed during the same time period, with no disinvestment process in place, but will receive the evidence arising from the intervention arm.

The mixed methods design combines quantitative and qualitative methodologies for the data collected and their analysis. Quantitative methods will be used to collect data for the rate of use of mobilisation alarms and other falls prevention strategies, resources allocated to the implementation of these strategies, and the clinical outcomes for participating wards. A narrative inquiry approach will be used to collect data regarding stakeholder acceptability of the disinvestment process; stakeholders will include health professionals and patients.

This study will also be a non-inferiority trial, this means we will try to prove that the removal/reduction of mobilisation alarms will not result in worse clinical outcomes. Therefore, a non-inferiority margin will be agreed upon with all health services in the intervention arm. The margin will be a specific rate of falls (averaged across all health services) that is just below the usual average rate of falls that is deemed unacceptable. For example, if the average number of falls that occur across Victoria is Y per week, then 150% more than Y falls per week while alarms are reduced/removed will see a stop to the entire project.

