# Results, Outcomes and Future Plans

Data will be regularly audited by an independent monitoring committee, comprising of two research team members ([name] and [name]) and one representative from each of the intervention arm health services in the study. This will ensure that each health service has access to study results as they arise. Each ward that participates in the study will be debriefed at the end of the intervention period and after the conclusion of all data collection regarding overall findings.

A number of scientific papers will be written to address each of the research aims already presented. These will be submitted to high-impact peer-reviewed journals in the area of health and medicine for publication.

The data obtained from this study may be used for research purposes not addressed in the current proposal. This study will be a large-scale multi-centre trial, therefore the results may be used as normative or reference data for other studies in the disciplines of health and falls prevention.

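### The protocol does not fix when the non-inferiority margin for falls is agreed, and its wording allows this to happen after post-crossover falls data have been seen

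*Protocol*

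**What the plan says.** Three places in the protocol bear on this point.

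- **Background** treats margin and stopping rule as linked: "non-inferiority margin stopping rules will be set to ensure maximum safety". It then lists, as a benefit of the design, that participating health professionals and service managers "contribute to the determination of stopping-rules during the trial".
- **Methodological Approach** gives the purpose, "we will try to prove that the removal/reduction of mobilisation alarms will not result in worse clinical outcomes", and says "a non-inferiority margin will be agreed upon with all health services in the intervention arm". It describes the margin as a falls rate averaged across services. The only number is an example in terms of an unspecified Y: "then 150% more than Y falls per week while alarms are reduced/removed will see a stop to the entire project". No time point is given for the agreement.
- **Results, Outcomes and Future Plans** places one representative of each intervention-arm service on the monitoring committee and adds: "This will ensure that each health service has access to study results as they arise".

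Outcome Measures and Data Collection (Table 1) names the rate of falls as the primary clinical outcome. Procedures has falls collected weekly, with pairs of wards crossing over month by month.

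**The concern.** A non-inferiority conclusion has a known error rate only if the margin was chosen without knowledge of the outcome. Here the parties who agree the margin are also the parties who see the accruing results, and the one phrase about timing puts the work during the trial. If the margin is settled after falls in the early wards are known, a reader of the final report cannot tell whether it reflects a prior judgement of what is tolerable or was chosen to fit the data. That would undermine the trial's main safety inference, and it cannot be repaired after the data have been seen.

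The point is about when the margin is fixed. It would remain whatever value is chosen and however the committee is made up.

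**Working it through.** **1. Is there a figure to reproduce?** Not for the margin, because none is stated. The ward numbers in Data Analysis concern alarm use: 15 per group, times a design effect of 1 + (3 − 1) × 0.10 = 1.2, gives 18, as stated. The falls power statement (86% for a 10% relative difference) concerns detecting a difference and uses no margin. So no number elsewhere in the protocol fixes the margin indirectly.

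**2. The sections side by side.**

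| Question | Answer in the protocol | Section |
|---|---|---|
| Are margin and stopping rule linked? | Yes, by phrase and by example | Background; Methodological Approach |
| Who contributes to the stopping rules? | Health professionals and service managers | Background |
| Who agrees the margin? | All intervention-arm services | Methodological Approach |
| When are stopping rules determined? | Literally, during the trial | Background |
| When is the margin agreed? | Not stated | Methodological Approach |
| Who sees accruing results? | The same services | Results, Outcomes and Future Plans |
| Is anything fixed before the first crossover? | Not stated | – |

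Eighteen wards in pairs make 9 steps. After the first step 2 wards have crossed and 16 have not, and falls arrive weekly. Post-crossover data therefore exist for most of the 9-month intervention period.

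**3. How much the margin matters (illustration only).** Inputs from Data Analysis: baseline 8 falls per ward-month, SD 4, ICC 0.63. Assumptions: 18 wards, 9 steps of 2, 10 monthly periods, a Hussey–Hughes model, a normal approximation, one-sided 2.5%, and a true excess of 10% of 8 = 0.8 falls per ward-month.

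Variance = Iσ²(σ² + Tτ²) / [(IU − W)σ² + (U² + ITU − TW − IV)τ²], where U is the number of intervention ward-months, W the sum over months of the squared number of wards under intervention, and V the sum over wards of the squared number of intervention months. Here I = 18, T = 10, U = 90, W = 1140 and V = 570, so the two brackets are 480 and 2640.

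- SD 4 taken as the total SD: τ² = 0.63 × 16 = 10.08 and σ² = 0.37 × 16 = 5.92. Variance = 11,372.1 / 29,452.8 = 0.386; SE = 0.62.
- SD 4 taken as the between-ward SD: τ² = 16 and σ² = 16 × 0.37 / 0.63 = 9.40. Variance = 0.613; SE = 0.78.

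Chance of claiming non-inferiority = Φ((margin − 0.8)/SE − 1.96):

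| Margin (falls per ward-month) | As % of 8 | SE 0.62 | SE 0.78 |
|---|---|---|---|
| 0.8 | 10% | 2.5% | 2.5% |
| 1.2 | 15% | 9% | 7% |
| 1.6 | 20% | 25% | 17% |
| 2.0 | 25% | 49% | 33% |
| 4.0 | 50% | over 99% | 98% |

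The protocol's own example shows how wide the open range is. If Y is set to the baseline of 8 per ward-month (an assumption, since Y is left undefined), 150% more than Y is 8 × 2.5 = 20, an excess of 12, while 150% of Y is 8 × 1.5 = 12, an excess of 4.

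The table shows that the conclusion depends on the margin. It does not forecast an error rate for this trial.

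**The case against.** The strongest reply is that the key sentence in Background is grammatically broken: a word is missing, and the timing phrase may attach to the rules (rules that operate during the trial) and not to their determination. Background is also introductory prose, while the procedure is in Methodological Approach. There the margin is set against the usual falls rate, with Victoria as the example benchmark and not accruing trial data, and a limit that halts the project when exceeded presupposes that the limit exists. This stands as far as it goes, so the adverse reading is permitted and not proved. But no sentence states the milder reading, and Methodological Approach gives no date that would settle the matter.

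A reader might infer more than the text supports:

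- *That services may revise the threshold, or that one service could tighten or loosen it.* No section provides for revision. Access to results is not authority over the margin, and agreement is required with all intervention-arm services.
- *That a safety stop is valid only if fixed blind to outcome.* This is too strong. Safety monitoring commonly involves judgement on accruing data. Prior fixing is essential for the margin used in the conclusion.
- *That one figure gives the false-claim rate.* Each entry in the table is an error rate only if the excess of 0.8 is judged unacceptable. If the wider margin were the right one, the same entry would be power.

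It may also be said that a statistical analysis plan could fix the margin. It could, but the Background wording would then contradict it and would still need amending.

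**Conclusion.** The concern holds in a limited form. The protocol links the margin to the stopping rules, places the determination of those rules during the trial on a literal though ambiguous reading, leaves the margin undated and without a value, and shows accruing results to the services that must agree it. The margin used for the conclusion on falls could therefore be settled with post-crossover data in view, and the false non-inferiority rate would then be uncontrolled. The documents do not show that this is intended or that it will happen.

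The size cannot be given as one number. It depends on the margins compared, the standard error and the true excess, and all of these had to be assumed here. The direction does not depend on them: for any given true excess, a wider margin makes the claim easier. The correction is cheap and has value only if made before the first crossover.

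**What to change.** Amend Background and Methodological Approach to say that the margin used for the non-inferiority conclusion is agreed with the intervention-arm health services, dated and recorded before the first pair of wards crosses over and before any post-crossover falls data are released, and is not changed afterwards.

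State that this inferential margin is separate from the safety stopping rule. Reconcile Background, Methodological Approach, and Results, Outcomes and Future Plans on when and by whom the stopping rule is set. The content of that rule is for those responsible for it and is not proposed here.

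The cost is a change of wording and one agreement meeting, which can fall within the 1-month baseline period already planned. The small downside is that services cannot renegotiate the margin once the trial is under way; their contribution to setting it is kept.

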## Research Aims

1. Examine the effectiveness of a disinvestment strategy implemented through a randomised stepped-wedge design in facilitating practice change in mobilisation alarm use.
2. Examine the sustainability of disinvestment outcomes.
3. Understand stakeholder acceptability, the mechanisms of impact and sustainability of the disinvestment process.
4. Examine the economic impact of disinvestment in mobilisation alarm use.

## Expected Outcomes

Based on pilot study results (Brusco et al., 2021), we hypothesise that removal and/or reduced use of mobilisation alarms can be achieved for hospital wards that understand and accept the evidence and the study’s conditions. During the disinvestment period, there will not be an increase in the number of falls or falls with adverse events in hospital wards. Sustainability of the practice following the end of the disinvestment period is unknown, and the findings of the proposed study will shed light on this matter.

It is anticipated that a range of responses will be gathered from stakeholders with regards to the application of disinvestment in a hospital setting. These responses may range from positive to negative, and the insight provided by these responses will identify health professionals' knowledge, beliefs, and attitudes that can facilitate or be barriers to the disinvestment process.

# Project Design

## Research Project Setting

This project will be carried out in 36 wards across at least 7 public and private health services in Victoria, with a portion of the data collection to be potentially completed online in compliance with COVID-safe guidelines. The process of disinvesting from mobilisation alarms will be conducted in acute and sub-acute hospital wards that meet inclusion criteria, with data to be collected by an onsite staff on a regular basis. Workshops and interviews will be conducted with staff from participating wards at 4 time points during the duration of the study; these will have the options to be completed online via the zoom.us platform for interviews and video sharing for workshops to minimise COVID-19 infection risk.

## Methodological Approach

This will be a concurrent, nested, randomised stepped-wedge study with a mixed methods and non-inferiority design (Figure 1). Half of the wards (n=18) will be assigned to the intervention arm, the other half to the control arm. All wards in the intervention arm will begin under the same “usual care” condition, pairs of wards will begin the disinvestment condition at different time points, which will allow for comparisons of the ward with itself under different conditions: a) usual care of utilising the mobilisation alarms, and b) removing or reducing its use. Randomisation will determine whether each ward undergoes a removed or reduced mobilisation alarm condition, and the timing at which they phase into this condition. All wards in the control arm will be observed during the same time period, with no disinvestment process in place, but will receive the evidence arising from the intervention arm.

The mixed methods design combines quantitative and qualitative methodologies for the data collected and their analysis. Quantitative methods will be used to collect data for the rate of use of mobilisation alarms and other falls prevention strategies, resources allocated to the implementation of these strategies, and the clinical outcomes for participating wards. A narrative inquiry approach will be used to collect data regarding stakeholder acceptability of the disinvestment process; stakeholders will include health professionals and patients.

This study will also be a non-inferiority trial, this means we will try to prove that the removal/reduction of mobilisation alarms will not result in worse clinical outcomes. Therefore, a non-inferiority margin will be agreed upon with all health services in the intervention arm. The margin will be a specific rate of falls (averaged across all health services) that is just below the usual average rate of falls that is deemed unacceptable. For example, if the average number of falls that occur across Victoria is Y per week, then 150% more than Y falls per week while alarms are reduced/removed will see a stop to the entire project.

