## Data Analysis

A reduction in the proportion of wards with high bed alarm use from 100% to 50% requires 15 wards per group to achieve 80% power with a two-tailed alpha of 0.05. The nesting of wards within health services (3 wards per service on average) requires adjustment for this design effect. Our disinvestment pilot study (Brusco et al., 2021) identified an intra-class correlation (ICC) of bed alarm use of 0.10, indicating we require 18 wards per group nested within the 6 health services. With this sample size, the intervention will have 86% power to detect a 10% relative difference in fall rates with a mean baseline of 8 falls (standard deviation=4) per month per ward, and an ICC of fall rates between wards of 0.63 based upon 1000 bootstrap power analysis simulations (Stata MP version 14.0).

Participating wards will be matched by type (acute, subacute) into clusters. Wards in each cluster will undergo the same period of intervention, allowing for comparison of varying degrees of disinvestment. Falls and alarm use rate across time will allow for the examination of the feasibility of disinvesting mobilisation alarms and its effects on falls rate and whether these effects can be sustained.

The content of post-workshop interviews and recordings of interviews with health service staff will be thematically analysed. The software NVivo will be used to aid in the coding, linking, categorising, and theme identification. Interview transcripts will be analysed independently by at least two researchers.

The cost-benefit analysis is calculated by summing the costs of the benefits and then subtracting the costs of implementation. The primary cost-benefit analysis will include the direct and indirect benefits, the secondary cost-benefit analysis will only include the direct benefits. Data will be analysed and presented as a total across the six participating health services as well as individually for each health service. Reporting for each health service individually will provide data on the range of implementation costs borne by the different health services. Average cost per health service will be reported as a mean value with a standard deviation, and the costs for the different health services will be compared with an independent t-test, where p<0.05 will be used to determine statistical significance.

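### The non-inferiority margin is merged with the project stopping threshold, and the falls power calculation is tied to neither

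*Protocol*

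**What the plan says.** Protocol, Methodological Approach, states the objective: "This study will also be a non-inferiority trial, this means we will try to prove that the removal/reduction of mobilisation alarms" will not lead to worse clinical outcomes. Rate of falls is the primary clinical outcome in Table 1.

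Four statements bear on how that objective would be judged.

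- **Background** uses one term for two things: "non-inferiority margin stopping rules will be set to ensure maximum safety".
- **Methodological Approach** leaves the value open ("a non-inferiority margin will be agreed upon with all health services in the intervention arm") but fixes its form: "The margin will be a specific rate of falls (averaged across all health services) that is just below the usual average rate of falls" regarded as unacceptable. The one numerical illustration, introduced as an example with Y the Victorian weekly average, is a stop: "then 150% more than Y falls per week while alarms are reduced/removed will see a stop to the entire project".
- **Data Analysis** claims "86% power to detect a 10% relative difference in fall rates", with a baseline mean of 8 falls per ward per month, SD 4 and ICC 0.63. It mentions no margin.
- **Background** also says that the approach "gives participating health professionals and service managers to contribute to the determination of stopping-rules during the trial".

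**The concern.** A non-inferiority margin is the largest true worsening that the final analysis must rule out. It applies to the contrast between intervention and usual care. A safety stop is a level of observed events at which the project halts. The two answer different questions and are normally far apart, because a stop is meant to catch gross harm.

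The protocol gives a single definition for both, in a form that suits the stop. An absolute rate judged against a state-wide average also makes no use of the within-ward comparison that the stepped-wedge design is built to provide. The falls power then addresses a third question, detecting a difference. Failing to detect a difference does not show non-inferiority.

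At stake is the main safety conclusion, that alarms can be withdrawn without more falls. As written, the criterion for that conclusion is unclear, and so is its error rate.

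**Working it through.** **1. The plan's own falls power.** Inputs from Data Analysis: mean 8, 10% difference = 0.8 falls per ward-month, SD 4 (variance 16), ICC 0.63. This gives between-ward variance 0.63 × 16 = 10.08 and within-ward variance 0.37 × 16 = 5.92. From Procedures: 18 wards stepping in pairs, 1 baseline month plus 9 intervention months.

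In a linear stepped-wedge model with ward random effects, power = Φ(0.8/SE − 1.96):

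- with month effects, SE 0.621: power 25%;
- without month effects, SE 0.419: power 48%.

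The stated 86% would need SE = 0.8/(1.96 + 1.08) = 0.263. I could not reproduce it. The simulation model behind it is not described, so this is non-reproduction and not a proven error. All three SEs are carried forward.

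**2. The illustrated threshold on the same scale.**

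- Literal reading: Y + 1.5Y = 2.5Y. On a baseline of 8 this is 20 falls, an allowed excess of 12.
- Looser reading: 1.5Y = 12 falls, an allowed excess of 4.
- Difference used for power: 0.8. The ratios are 12/0.8 = 15 and 4/0.8 = 5.

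These are different quantities and need not be equal. The sizes only show how much turns on which figure is taken as the margin.

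**3. Chance of declaring non-inferiority if the threshold were the margin.** Criterion: upper two-sided 95% limit below the margin. P = Φ((allowed excess − true excess)/SE − 1.96).

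| Margin | True rise | SE 0.621 | SE 0.419 | SE 0.263 |
|---|---|---|---|---|
| 2.5Y (12) | 50% (4) | 1.00 | 1.00 | 1.00 |
| 1.5Y (4) | 25% (2) | 0.90 | 1.00 | 1.00 |

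Example: (4 − 2)/0.621 − 1.96 = 1.26, and Φ(1.26) = 0.90.

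**4. The same check on the rate-ratio scale.** A Poisson simulation of the 18 wards over 10 months, with ward and month effects, gave an SE of the log rate ratio of about 0.093. It used between-ward variance 8 plus Poisson variance 8, an ICC of 0.50 and not the stated 0.63.

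- Margin 2.5, true ratio 1.5: ln(2.5/1.5)/0.093 − 1.96 = 3.53, so P is above 0.99.
- Margin 1.5, true ratio 1.25: ln(1.5/1.25)/0.093 − 1.96 = 0.00, so P = 0.50. Simulation gave 54%.

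**5. If 10% were the margin instead.** With no true change, P = Φ(0.8/SE − 1.96), the same expression as in step 1: 0.25, 0.48 or 0.86. Taking the protocol's 86% at face value, a 10% margin would have 86% power. The protocol does not say that 10% is the margin.

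**The case against.** The 150% figure is only an example, and the margin is still to be agreed with the services. That is correct: nothing in the protocol adopts 2.5Y or 1.5Y. What stands is the form of the definition, which is not part of the example. Margin and stop are one object, stated as an absolute average rate, and no deadline is given for agreeing it.

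A reader might infer that the trial could call a doubling of falls non-inferior. The documents do not support that as a finding. It needs the example to become the margin and its literal reading to be the intended one; under 1.5Y a doubling would practically never pass. It also ignores the stop itself. Under a doubling, weekly counts could cross the threshold and halt the project before any final analysis. How often depends on how the weekly rule is applied, which the protocol does not say.

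A reader might also infer that the margin will be set on accruing data. The Background sentence is ungrammatical, and its closing words may describe rules that operate during the trial and not rules settled during it. The risk is still open. The services that agree the margin also sit on the monitoring committee and have access to results as they arise (Results, Outcomes and Future Plans), and no text requires the margin to be fixed first.

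Nor can the falls test be called two-sided as a matter of fact. Two-tailed alpha of 0.05 is stated only for alarm use.

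Finally, the detailed test might be left to an SAP. That covers the model and its covariates. It does not cover a protocol that defines its margin as a stopping level and powers falls without reference to any margin.

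**Conclusion.** The point holds as wrong as written. Background and Methodological Approach merge the margin with the project stop, on a scale that is not the intervention versus usual-care contrast. Data Analysis gives a falls power that is not tied to the declared non-inferiority claim.

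On size: if the illustrated threshold were used as the margin, a true 50% rise would pass almost always under 2.5Y. A true 25% rise would pass with probability from about 0.5 to nearly 1 under 1.5Y, depending on the standard error. These figures assume that the example is adopted, that the trial runs to completion, that the criterion is the upper two-sided 95% limit, and that the true SE is near one of those tried. The textual conflict rests on none of these assumptions, nor on whether the 86% can be reproduced.

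**What to change.** - **Background and Methodological Approach:** define the non-inferiority margin and the safety stopping rule separately. State the margin as a rate ratio of intervention to usual care, fixed in writing before the first pair crosses over. Reword the Background sentence on stopping rules so that the margin cannot be set on accruing data.
- **Methodological Approach:** declare non-inferiority only if the upper confidence limit of that ratio is below the margin. Say whether the illustrated threshold means 1.5Y or 2.5Y, and whether the reference is the Victorian average or the participating services.
- **Data Analysis:** replace the power to detect a 10% difference with power for the non-inferiority test under a true ratio of 1, with alpha and sidedness stated.

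The sponsor and services choose the margin and the stopping level; none is proposed here. The three sections must be reconciled. The cost is wording in those sections, one rerun of the power simulation, and agreement on a margin before the first crossover.
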